## Data analysis

8

### Sample size and statistical power

8.1

The optimal sample size is calculated based on a statistical power of 90% and a significance level of 0.05 (two-tail). To calculate the sample size, we have estimated the incidence of significant improvement in primary or secondary outcome measures to be 75% in group 1 (individuals on the KD) and 40% in group 2 (individuals on the AGHE diet). We will aim for a 1:1 enrolment ratio.

Using these values, our estimated sample size is 80 individuals (40:40), however, considering a dietary intervention attrition rate of at least 20%, we will aim to recruit 100 individuals (50:50).

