### Data analysis plan

8.2

The analysis of the biological samples will be conducted by biomedical staff at James Cook University overseen by the James Cook University Specialist in Clinical Biochemistry and Clinical Research Coordinator of the Australian Institute of Tropical Health and Medicine. This will follow standard analytic pipelines established in these units.

We predict that analyses of observed data will be largely descriptions of response, adherence, and distributions of values. Simple correlations between study parameters will follow standard statistical methods and the assistance of a statistician has been sought to define the statistical plan before the research plan is finalized. Software packages will include SPSS (v28) and *R* (v4.2.1).

In line with Burgess et al. (62) and many other modern statisticians who have described the procedure of hypothesis testing on baseline characteristics as unnecessary and potentially harmful (63), we will present the distribution of baseline information of intervention groups in a simple table, allowing readers to compare the extent of similarities, each with a mean and percentage value for both treatment groups separately. Additional co-variables may likely be at play, especially socioeconomic status, BMI, and severity of illness. Therefore, a degree of covariate adjustment is expected at the statistical calculation stage. Logistic regression and Analysis of Covariance are likely going to be incorporated into the data analysis plan.

For our quantitative endpoints (e.g., on psychiatric scales and metabolic parameters), linear mixed effects (LME) models will be used to compare the intervention and control groups. If normality cannot be assumed, a logarithmic transformation of the response variable will be performed to meet the assumption of normality. Mixed-effect logistic regression will be used for binary endpoints and longitudinal data. If data normality cannot be achieved, a comparison of our variables of interest between groups will take place using non-parametric tests, e.g., the Mann–Whitney U test. All analyses will be conducted by an intention-to-treat (ITT) approach using all available data, including those who were not to complete the study. Patient data will be analyzed per their original treatment allocation. All data analyses will be performed using 5% significance levels and audited by several members of the research team to ensure accuracy before submission.

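### The stated 90% power is for an undefined yes/no improvement across primary or secondary measures, so it is not shown to apply to any listed primary comparison

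*Protocol article*

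**What the plan says.** **Sample size (section 8.1).** The calculation uses "a statistical power of 90% and a significance level of 0.05 (two-tail"). The quantity compared is a proportion: "we have estimated the incidence of significant improvement in primary or secondary outcome measures to be 75% in group 1" (the ketogenic diet) and "40% in group 2 (individuals on the AGHE diet"). Allocation is equal, and the result is "our estimated sample size is 80 individuals (40:40"). Then, "considering a dietary intervention attrition rate of at least 20"%, the plan is that "we will aim to recruit 100 individuals (50:50").

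**Outcomes (Abstract, Outcomes).** Six instruments are listed as primary: PANSS, the Young mania scale, the Beck inventory, the WHO disability schedule, the affect lability scale and the Cambridge cognitive battery. A separate secondary set covers weight, blood pressure, liver and kidney tests, lipids and insulin resistance. Neither list contains a yes/no improvement outcome. Sections 3 to 5 describe scores and laboratory values and give no responder cut-off.

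**Analysis (section 8.2).** For quantitative endpoints, with psychiatric scales and metabolic parameters given as examples, "linear mixed effects (LME) models will be used to compare the intervention and control groups". Mixed-effect logistic regression is foreseen for binary endpoints, but none is named.

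**The concern.** A power statement is informative only when tied to the comparison that will be made. Here there are three mismatches.

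- **Event and outcome list.** The powered event does not appear among the primary or secondary outcomes.
- **Event and aim.** Because primary and secondary measures are pooled, weight loss or a better lipid value could count as success. The 75% and 40% then need not describe psychiatric or cognitive benefit at all.
- **Event and analysis.** The event is binary, while the scales are to be compared as quantitative scores.

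The section does not say which instrument counts, how much change is needed, at which visit, or whether one improved measure is enough. No mean difference or SD is given for any scale.

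What is at stake is how the result is read. Readers and the ethics committee see 90% power with no outcome attached to it. A null result on the PANSS or the Beck inventory could be taken as well-powered evidence of no effect. A metabolic gain could be taken as meeting the design target.

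**Working it through.** **Inputs from section 8.1:** rates 0.75 and 0.40; two-sided alpha 0.05 (z = 1.960); power 90% (z = 1.2816); allocation 1:1; attrition at least 20%.

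**Step 1. Reproduce the plan's figure.** For two proportions with pooled variance under the null and no continuity correction, the mean rate is (0.75 + 0.40)/2 = 0.575, and

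n per arm = [1.960 × √(2 × 0.575 × 0.425) + 1.2816 × √(0.75 × 0.25 + 0.40 × 0.60)]² / 0.35²

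= [1.960 × 0.6991 + 1.2816 × 0.6538]² / 0.1225 = [1.3702 + 0.8379]² / 0.1225 = 39.8.

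This rounds up to 40 per arm, 80 in all, with power 90.1%. Recruitment is 80/(1 − 0.20) = 100. Both stated figures reproduce, so there is no arithmetic error.

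**Step 2. What 40 per arm gives for a quantitative scale.** The documents give no difference or SD, so the true difference d, in SD units, is an assumption shown as a range. For an unadjusted two-sample t comparison at one visit (noncentral t, 78 degrees of freedom, noncentrality d × √(40/2)), two-sided 5%:

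| True difference (SD) | Power, 40 per arm |
|---|---|
| 0.4 | 42% |
| 0.5 | 60% |
| 0.63 | 80% |
| 0.73 | 90% |

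As a check, the normal approximation gives (1.960 + 1.2816) × √(2/40) = 0.72 SD for 90% power and (1.960 + 0.8416) × √(2/40) = 0.63 SD for 80%.

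**Step 3. Allow for baseline adjustment.** If the baseline score correlates r with the final score, adjustment multiplies the residual SD by √(1 − r²). The documents give no r. At an assumed r of 0.5, the difference detectable with 90% power is 0.734 × √0.75 = 0.64 SD. At an assumed r of 0.7 it is 0.734 × √0.51 = 0.52 SD.

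**Step 4. Allow for higher attrition.** One hundred recruited leave 80 only if attrition is exactly 20%, whereas the plan treats 20% as a minimum. At an assumed 30%, 100 × 0.70 = 70 remain, 35 per arm. The unadjusted difference for 90% power is then 0.79 SD. The stated 75% against 40% comparison would have 86% power.

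**Step 5. What the 75% and 40% would mean on a single scale.** Suppose both rates referred to one scale whose change is normal with equal SDs, dichotomised at a common cut-off. The implied difference is the sum of the normal quantiles for 75% and 60%: 0.674 + 0.253 = 0.93 SD. With 40 per arm, the undichotomised comparison would have 98% power.

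Steps 2 and 5 bracket the problem. The same 80 evaluable participants could be underpowered or amply powered for a given scale, and section 8.1 does not say which case it claims.

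**The case against.** The strongest reply is that nothing here shows the trial to be underpowered. A reader might infer from the mismatch that no primary comparison has 90% power. The documents do not support that. They give no effect size for any scale, so power on each scale is unknown rather than shown to be low. Under the single-scale reading in step 5, power would exceed the stated figure. This part of the reply stands.

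A reader might also take the event as improvement on any one of the listed measures and work back to low rates on each scale. Section 8.1 does not say that one measure suffices. Power for dichotomised scale-by-scale tests would also describe an analysis that section 8.2 does not plan for the scales. No such figure is relied on here.

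The 0.73 SD benchmark is an unadjusted comparison. The plan foresees mixed models over repeated visits, covariate adjustment and use of all available data, including from people who do not complete. These should lower the detectable difference, so 0.73 SD should be labelled as unadjusted. This also stands.

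Finally, section 8.2 allows for binary endpoints, and an analysis plan that is not shown may define a responder. That would supply a definition, but it would not change the event for which 80 was calculated, nor remove the written pooling of primary and secondary measures. The attrition point is minor: the allowance is correct at 20%, and 30% is an assumption made here.

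**Conclusion.** The point holds as a mismatch between the sample-size basis and the endpoints. The 40 per arm and the 100 recruited are computed correctly. The 90% belongs to an undefined binary event that mixes primary with secondary measures, is not a listed outcome, and does not match the analysis planned for the scales. It is therefore not shown to apply to any primary comparison.

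For a quantitative scale, 40 evaluable per arm gives 90% power at 0.73 SD, 80% at 0.63 SD and about 60% at 0.5 SD. These figures assume a single unadjusted two-sided 5% comparison at the final visit. The 90% figure moves to about 0.64 SD with an assumed baseline correlation of 0.5, and to 0.79 SD, unadjusted, with an assumed 30% attrition.

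**What to change.** Keep the recruitment target of 100. In section 8.1, delete *or secondary* and name the primary scale to which the power statement refers. Suggested text:

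> With 40 evaluable participants per arm and a two-sided 5% level, an unadjusted comparison of [named primary scale] at T3 has 90% power for a difference of 0.73 SD and 80% power for 0.63 SD (about 60% at 0.5 SD). Baseline adjustment lowers the detectable difference, for example to about 0.64 SD for 90% power if the baseline correlation is assumed to be 0.5. If attrition is 30% (35 per arm), the unadjusted difference for 90% power is 0.79 SD.

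If the 75% against 40% responder comparison is kept, define it on that one scale with a numeric cut-off and a visit, and list it as an outcome.

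No participants are added. The stated power becomes less favourable, and the sponsor must choose one scale from the six instruments. That is a substantive decision as well as an edit to the text.

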### Data analysis plan

8.2

The analysis of the biological samples will be conducted by biomedical staff at James Cook University overseen by the James Cook University Specialist in Clinical Biochemistry and Clinical Research Coordinator of the Australian Institute of Tropical Health and Medicine. This will follow standard analytic pipelines established in these units.

We predict that analyses of observed data will be largely descriptions of response, adherence, and distributions of values. Simple correlations between study parameters will follow standard statistical methods and the assistance of a statistician has been sought to define the statistical plan before the research plan is finalized. Software packages will include SPSS (v28) and *R* (v4.2.1).

In line with Burgess et al. (62) and many other modern statisticians who have described the procedure of hypothesis testing on baseline characteristics as unnecessary and potentially harmful (63), we will present the distribution of baseline information of intervention groups in a simple table, allowing readers to compare the extent of similarities, each with a mean and percentage value for both treatment groups separately. Additional co-variables may likely be at play, especially socioeconomic status, BMI, and severity of illness. Therefore, a degree of covariate adjustment is expected at the statistical calculation stage. Logistic regression and Analysis of Covariance are likely going to be incorporated into the data analysis plan.

For our quantitative endpoints (e.g., on psychiatric scales and metabolic parameters), linear mixed effects (LME) models will be used to compare the intervention and control groups. If normality cannot be assumed, a logarithmic transformation of the response variable will be performed to meet the assumption of normality. Mixed-effect logistic regression will be used for binary endpoints and longitudinal data. If data normality cannot be achieved, a comparison of our variables of interest between groups will take place using non-parametric tests, e.g., the Mann–Whitney U test. All analyses will be conducted by an intention-to-treat (ITT) approach using all available data, including those who were not to complete the study. Patient data will be analyzed per their original treatment allocation. All data analyses will be performed using 5% significance levels and audited by several members of the research team to ensure accuracy before submission.

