## Randomization

6

For this study, stratified randomization will be used. We will stratify by assuming eight groups based on the following criteria: diagnosis (schizophrenia or bipolar disorder), gender (male or female), and duration of illness (DOI; more or less than 5 years). Groups will be divided as demonstrated in Figure 2.

Each of the stratified groups will be randomly allocated into either KD or AGHE. The allocation will be concealed from the investigators and will only be known by the Clinical Research Coordinator. Each subsequent entry to each stratum will be sequentially followed, thereby creating a stratified, random allocation. Recruitment for this trial will be continuous for 18 months or until the required participation number has been reached.

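### Covariates are left to be settled at calculation; the three stratification factors are not named and the handling of each outcome's T1 value is not fixed

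*Protocol article*

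**What the plan says.** The Protocol article, section 6 (Randomization), states: "For this study, stratified randomization will be used". The factors are diagnosis (schizophrenia or bipolar disorder), gender, and duration of illness above or below 5 years, giving eight strata.

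Section 8.2 (Data analysis plan) first describes a baseline table without significance tests. It then says: "Additional co-variables may likely be at play, especially socioeconomic status, BMI, and severity of illness". From this it concludes that "a degree of covariate adjustment is expected at the statistical calculation stage". Logistic regression and analysis of covariance are described as likely. Linear mixed effects (LME) models are the stated method for quantitative endpoints, with no fixed effects listed. The fallback if normality fails is a non-parametric test such as Mann–Whitney, which in its ordinary form carries no covariates.

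Section 2.1.2 (Assessments) has the psychiatric, cognitive and metabolic measures taken at T1, before randomisation. The stratification factors and baseline values are therefore all known before allocation.

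**The concern.** Two things are at stake.

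**Precision.** The randomisation uses three factors, and the covariate passage points to three others. If the factors or the T1 value are prognostic and do not enter the model, confidence intervals are wider than they need to be. Naming an LME does not settle this. Depending on how T1 is handled, the same label covers analyses of clearly different precision.

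**Freedom of choice.** Three optional covariates allow eight models. The only timing given for the choice is when results are calculated, and nothing in section 8.2 says the set will be locked before allocation is known to the analyst. If the most favourable model is the one reported, the 5% level no longer holds. The abstract lists six primary instruments, so the choice could recur for each.

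**Working it through.** **1. The plan's own figure.** Inputs from section 8.1: response 75% against 40%, two-sided 0.05, power 90%, 1:1 allocation, 20% attrition. With mean proportion 0.575:

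n per arm = [1.960·√(2·0.575·0.425) + 1.2816·√(0.75·0.25 + 0.40·0.60)]² / 0.35² = (1.370 + 0.838)² / 0.1225 = 39.8, so 40 per arm.

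The total is 80, power at 40 per arm is 90.1%, and 80/0.8 = 100. The stated numbers reproduce. The calculation is unadjusted and takes no credit for covariates.

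**2. Handling of the T1 value.** The documents give no SD or correlation, so I assume a 0.5 SD effect and a T1–T3 correlation ρ. The effective SD multipliers are:

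- T3 only: 1
- change from T1: √(2(1−ρ))
- baseline ANCOVA: √(1−ρ²)

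An LME with T1 as a response and free group means at T1 has the precision of the change score. If the T1 means are constrained equal, it has that of ANCOVA. Power = Φ(0.5 / (multiplier·√(2/40)) − 1.960).

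| ρ | T3 only | Change | ANCOVA |
|---|---|---|---|
| 0.3 | 60.9% | 47.2% | 65.0% |
| 0.5 | 60.9% | 60.9% | 73.3% |
| 0.6 | 60.9% | 70.5% | 79.8% |
| 0.7 | 60.9% | 82.3% | 87.9% |

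At ρ = 0.6 the ANCOVA multiplier is √0.64 = 0.80. The interval is then 1/0.80 = 1.25 times as wide for T3 only, and √0.80/0.80 = 1.118 times as wide for change. The formula is a normal approximation. Simulation with t-based tests gives slightly lower values at ρ = 0.6: about 60%, 68% and 78%.

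**3. Adding the stratification factors.** Simulation assumed 80 participants, eight strata of 10 split 5:5, ρ = 0.6 and stratum effects stable over time. Block size and stratum sizes are assumptions; section 6 gives neither.

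- Baseline ANCOVA, without and with strata: 77.6% and 78.5% power at R² = 0.1; 78.1% and 79.9% at R² = 0.2. Type I error without strata stays at 4.4–5.1% for R² from 0.1 to 0.3.
- Change from T1: 68–69% with or without strata, because a stable stratum difference cancels.
- T3 only, strata ignored: type I error 4.1% at R² = 0.10 and 2.9% at R² = 0.20, against 5.1% and 5.4% adjusted. Intervals are 5.5% and 12.1% wider.
- R² = 0: no gain and no loss.

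These simulated powers are good to a point or two.

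**4. Free choice of covariates.** Three optional covariates give 2³ = 8 models. Under no treatment effect with 80 participants, the chance that at least one model is significant is 8.3% for covariate R² of 0.02, 0.02 and 0.10; 11.1% for 0.05, 0.05 and 0.25; and 11.7% for 0.05, 0.05 and 0.36.

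**The case against.** The strongest reply is that the article lists no model terms at all, so nothing has been left out. Exact fixed effects usually belong in a statistical analysis plan, which is not shown. The article says a statistician's help has been sought for that plan. ANCOVA is named as likely and commonly carries the baseline value, severity of illness may itself mean the T1 score, and a longitudinal LME can hold T1 as a response. This stands. A reader might infer that the plan drops the strata and the baseline values, and the text does not support that.

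A reader might also infer that ignoring the strata pushes type I error down to 2–3% and costs a large share of power. That needs a T3-only analysis with strongly prognostic strata. Once T1 is in the model, the strata add a point or two at R² of 0.1–0.2. The strata and baseline losses overlap and cannot be added together.

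Nor does the document say that covariates will be picked after results by arm have been seen. Any adjustment is carried out when results are calculated. The 8–12% is what the wording permits, not what it announces.

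What the reply does not answer is that section 8.2 is not merely silent. It states when adjustment will be settled and which variables lead the list, and neither matches the randomisation in section 6.

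**Conclusion.** The point holds as one of an unfixed and poorly directed covariate rule. The larger statistical gain comes from entering the T1 value as a covariate: about 78% power against 68% for change from T1 and 60% for T3 only (0.5 SD effect, ρ = 0.6, 40 per arm). Against the change score the gain shrinks as ρ rises; against T3 only it grows. The stratification factors add little beyond that, to about 79–80% at R² of 0.1–0.2, and nothing if they are not prognostic. Locking the set removes a possible rise in type I error to about 8–12%, under the assumed covariate strengths and reporting of the most favourable model. No SD, R² or correlation in the documents narrows these ranges. The sample size of 80 evaluable and 100 recruited reproduces and is not undermined.

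**What to change.** Replace the covariate sentence in section 8.2 with:

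*Covariates are fixed before unblinding. Each LME includes treatment, visit, treatment-by-visit, the T1 value of the outcome, and diagnosis group, sex and duration of illness as used in randomisation; the treatment effect is the T3 contrast.*

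Four details go with it:

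- With T1 as a covariate, the responses are T2 and T3. For the cognitive battery, repeated only at T3, the model reduces to ANCOVA.
- Socioeconomic status and BMI move to one pre-specified sensitivity analysis.
- State which diagnosis level schizoaffective participants take. They are eligible under Table 1, but section 6 lists only schizophrenia or bipolar disorder.
- For mixed logistic models, state that the odds ratio is conditional on these covariates, because adding covariates changes the odds ratio being estimated.

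The cost is a few sentences and a few degrees of freedom. The stratification factors and T1 values are already collected before allocation.

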## Discussion

9

The rationale for this randomized controlled clinical trial is based on a converging line of evidence coming from recent studies showing a variety of brain bioenergetic abnormalities in schizophrenia and bipolar disorders, prior preclinical research demonstrating the efficacy of the ketogenic diet in animal models of schizophrenia, as well as recent encouraging results from case studies and pilot, single-arm clinical trials that indicate clear symptom improvement and better metabolic control in patients with serious mental illness on a ketogenic diet. We expect that the dietary metabolic interventions in our trial will result in beneficial changes in symptoms, everyday functioning, and overall metabolic health for our participants. The control diet, based on the AGHE guidelines, is likely superior in terms of its health effects compared to the participants’ usual dietary patterns because of its focus on incorporating whole grains, dietary fiber, plant-based proteins, and unprocessed food. We expect that the ketogenic metabolic therapy, with its targeted effect on brain and systemic energy metabolism, will result in further improvements in metabolic health, controlling psychiatric symptoms and improving overall functioning, above and beyond the control diet. In addition to establishing efficacy, our design will allow the assessment of the participant’s compliance with and adherence to a relatively restrictive dietary schedule that requires major deviations from their usual diet. This will be important for future dietary metabolic interventions in serious mental illness, where patients are generally perceived to be struggling with such challenges.

In case of demonstrated efficacy, it is crucial to understand the mechanism of action of this novel metabolic intervention to give informed advice to the psychiatric community on any potential change in clinical practice. Our trial will collect data from different domains, including systemic metabolism and inflammatory processes, autonomic nervous system activity, sleep patterns, and changes in the gut microbiome. Outcome measures from these systems, when correlated with improved psychiatric symptoms, cognitive functions, and overall daily functioning will inform us about the potential involvement of underlying mechanisms. With regards to mechanisms of action of dietary intervention, the possible mediating role of the gut microbiome is of primary importance as the ecosystem of the bacteria in the gastrointestinal system interacts with the consumed diet even before the different nutrients and other food-derived molecules get into the bloodstream (64–67). It is conceivable that some of the effects of the ketogenic metabolic therapy may be mediated by the gut microbiome, either directly through microbiome-derived metabolites that reach the brain or indirectly through changes in the enteric nervous system activity. We aim to establish such a role for the gut microbiome by demonstrating ketogenic diet-related changes associated with symptom improvement. Ketone bodies, beta-hydroxybutyrate, and acetoacetate are the metabolic products of the liver while on the ketogenic diet (36). Ketones have been shown to directly benefit brain bioenergetics (68, 69). The daily ketone monitoring will make it possible not only to confirm adherence to the ketogenic diet but also to correlate ketone levels with daily changes in the self-reported energy levels of the participants. Alterations in autonomic nervous system activity and sleep have been widely reported in schizophrenia (70) and bipolar disorders (71, 72). The ketogenic diet seems to be effective in influencing these functions. Therefore, the potential mechanistically important role of autonomic nervous system activity and sleep health can be uncovered by monitoring these functions using wearable devices before the introduction and at the end of the dietary intervention. Although human studies are rarely designed to include an experimental intervention that directly informs about exact mechanisms of action, the complex analysis of multiple, interacting systems will show biomarkers that are specifically modified by the treatment and associated with improvements in different symptom domains.

Our trial design has some limitations. Firstly, despite our best efforts to keep the overseeing psychiatrists blind to the dietary arm allocation of individual participants, we cannot rule out the possibility that some participants may disclose their diets during the psychiatric assessments in the middle or at the end of the trial. Also, an argument can be made that some of our motivated participants may have information about the expected benefits of the ketogenic metabolic therapy in their condition, which could conceivably introduce an expectation bias if assigned to the ketogenic arm of the trial. We will, however, obtain their daily blood ketone levels which can be correlated with the results of the psychiatric and cognitive assessment, and give an objective control measure to address the above limitations. Another possible limitation is that due to the nature of this clinical trial conducted in an outpatient setting, relying on the ability of the participant to adhere to a relatively restrictive dietary regime independently, the recruited participants will be better functioning than some other patients with serious mental illness, resulting in a self-selected study population. We acknowledge this limitation, but we argue that although we might be able to demonstrate better adherence in this self-selected group, it may be a strength of the trial to demonstrate symptom improvement in participants who may be somewhat better functioning already. Additionally, demonstrating adherence to a restrictive dietary regimen by a population with severe mental disorders in the community may in itself be regarded as a satisfactory outcome measure.

In conclusion, we expect this randomized controlled clinical trial to assess the feasibility, efficacy, and safety of ketogenic metabolic therapy in schizophrenia and bipolar disorder. To our knowledge, our proposed trial is the first of its kind worldwide. We hypothesize that this study will reveal improvements in symptoms, overall quality of life, and better metabolic functioning for our participants. Results from this trial may inform future studies on more specific mechanisms of action, as well as introduce a novel treatment modality to manage psychiatric disorders that would otherwise have been considered as long-term, debilitating conditions.

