### Stool collection

7.2

It will be optional for all participants to supply a stool sample at the start of the trial (prior to T1) and again at the end of the trial period (week 14) for the future analysis of changes in the fecal microbiome composition and its metabolites. The participant will be supplied with a self-collection kit during the Week 0 assessment, and they can collect the specimen at home at their earliest convenience. The kit can be posted to the research team.

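### The stated criterion for a gut-microbiome role, changed by the diet and associated with improvement, cannot establish mediation

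*Protocol article*

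**What the plan says.** Four places in the protocol article bear on this.

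- **Section 9, Discussion, on the microbiome:** "We aim to establish such a role for the gut microbiome by demonstrating ketogenic diet-related changes associated with symptom improvement". The role in question is a mediating one, which the same paragraph calls of primary importance.
- **Section 9, Discussion, on biomarkers generally:** the planned analysis is expected to show "biomarkers that are specifically modified by the treatment and associated with improvements in different symptom domains".
- **Section 8.2, Data analysis plan:** "Simple correlations between study parameters will follow standard statistical methods". No other method for relating markers to outcomes is named. The section does expect some covariate adjustment and mentions analysis of covariance, but ties neither to the marker analyses.
- **Section 7.2, Stool collection:** samples are optional, taken at the start and "again at the end of the trial period (week 14) for the future analysis of changes in the fecal microbiome composition". Hair (7.3) and wearable data (7.1) are likewise optional and limited to the start and week 14.

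The Discussion is more cautious elsewhere. Correlations across the systems studied "will inform us about the potential involvement of underlying mechanisms". The sentence containing the biomarker criterion begins "Although human studies are rarely designed to include an experimental intervention that directly informs about exact mechanisms of action". The conclusion adds: "Results from this trial may inform future studies on more specific mechanisms of action".

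**The concern.** Mediation means that the diet changes the marker and that the marker's change in turn changes the symptoms. The stated criterion tests the first link and then asks only for an association between marker and symptom change. The diet itself can supply that association. If it moves the marker and also, by another route, the symptoms, the two changes are correlated across participants although neither acts on the other. The correlation is then genuine, and the mechanistic reading of it is false.

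This matters most in the situation the paragraph has in mind. It opens on the case in which efficacy has been shown, and its criterion selects markers that the treatment has changed. Those are the two conditions under which a pooled correlation misleads. At stake is an inert marker being put forward as an established mechanism. The randomised comparison of diets is not at stake.

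**Working it through.** **The plan's own figure.** Section 8.1 gives 75% versus 40%, 90% power and two-sided 0.05. With pooled variance under the null:

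n per arm = [1.960·√(2·0.575·0.425) + 1.2816·√(0.75·0.25 + 0.40·0.60)]² / 0.35² = (1.370 + 0.838)² / 0.1225 = 39.8, so 40.

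This reproduces the stated 80, and 80/0.8 = 100 reproduces the recruitment target. The sample size is not in question. It supplies the n and the symptom effect used below.

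**Inputs**

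- n: 40 per arm (section 8.1). Because stool samples are optional, 20 per arm is also shown, as an assumption.
- Symptom effect dY: 0.93 SD, the latent shift implied by the response rates, z(0.75) − z(0.40) = 0.674 + 0.253. A smaller 0.5 SD is an assumption.
- Marker effect dM: 0.5 to 2 SD, an assumption. The article gives no figure.
- The marker has no effect on the symptom. Test level 5% (section 8.2), two-sided.

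**Arms pooled, uniform response to the diet.** With 1:1 arms and unit within-arm SD:

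r = (dM·dY/4) / √[(1 + dM²/4)(1 + dY²/4)]

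Example, dM = 2 and dY = 0.93: 0.464 / √(2 × 1.215) = 0.464/1.559 = 0.30.

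Share of 20,000 simulated trials with a significant correlation:

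| dM (SD) | r, dY 0.93 | 40/arm, dY 0.93 | 20/arm, dY 0.93 | r, dY 0.5 | 40/arm, dY 0.5 |
|---|---|---|---|---|---|
| 0.5 | 0.10 | 15% | 10% | 0.06 | 8% |
| 1.0 | 0.19 | 40% | 22% | 0.11 | 17% |
| 1.5 | 0.25 | 65% | 36% | 0.15 | 25% |
| 2.0 | 0.30 | 80% | 49% | 0.17 | 34% |

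If the diet has no symptom effect (dY = 0), the rate stays at 5%. With uniform response it is also 5% within the ketogenic arm alone or after adjustment for arm.

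**Adherence varying within the ketogenic arm.** Both diet effects are now multiplied by each participant's adherence (mean 1, coefficient of variation assumed), with 40 per arm and dY = 0.93. The marker is still inert.

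| Adherence CV | Ketogenic arm only, dM 1 / 1.5 / 2 | Adjusted for arm, dM 1 / 1.5 / 2 |
|---|---|---|
| 0.3 | 8% / 10% / 14% | 6% / 8% / 11% |
| 0.5 | 21% / 36% / 47% | 16% / 25% / 36% |
| 0.75 | 60% / 80% / 89% | 46% / 69% / 81% |

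Adjusting for arm removes the between-arm artefact but not the one that adherence creates.

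**Timing.** With one stool, hair or wearable measurement at each end, marker change and symptom change cover the same interval. Marker change cannot be seen to come first.

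**The case against.** Several points on the other side stand.

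- **Pooling is not stated.** A reader might infer that correlations across both arms will be run and false mechanisms reported. The article does not say so. The one correlation with a stated analysis set, that for ketosis level in the Abstract, is confined to the intervention group. The sentence on simple correlations is not tied to the microbiome aim, and the Discussion speaks of a complex analysis. The pooled rates therefore show what can happen, not what will.
- **The strong verb covers only the microbiome.** A reader might extend it to every marker. The other systems are said to bear on potential involvement. The general biomarker sentence uses the same criterion but claims association, not causation.
- **The remark on advising the psychiatric community is motivation.** It explains why mechanism matters if efficacy is shown. It does not commit the trial to act on a correlation.
- **Timing does not affect every marker.** Fasting blood is drawn at baseline, week 8 and week 14 (section 5), and the psychiatric scales are repeated at the same three visits (2.1.2). Early change in blood markers can be related to later symptom change.
- **Model detail may sit elsewhere.** A mediation or adjustment plan may be in an analysis plan not shown, so its absence is no finding here.

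These points narrow the concern without removing it. The criterion is stated, it is insufficient with pooled arms or within one arm, and the cautious phrases do not correct the sentence that claims to establish a role. They conflict with it.

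**Conclusion.** The concern holds in limited form. Being changed by the diet and associated with improvement cannot establish that the gut microbiome mediates the effect, and the claim to do so contradicts the article's own hedges. Certainty that false mechanisms will be reported is not supported. An inert marker passes the association step in 15% to 80% of trials if arms are pooled at the planned size and effect, in 8% to 34% with a 0.5 SD symptom effect, and in 5% within arm if response to the diet is uniform. With varying adherence the rate is 8% to 89% in the ketogenic arm and 6% to 81% after arm adjustment. The marker effects, the smaller symptom effect, the adherence variation and the 20-per-arm case are assumptions. The 0.93 SD is a latent-scale translation of the response rates. Severity is low: this is Discussion wording about an optional, future analysis, and the randomised efficacy comparison is untouched.

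**What to change.** 1. For marker-outcome analyses, replace simple correlations with a regression of outcome change on marker change that includes treatment arm, baseline marker and baseline outcome, using both arms.
2. Add adherence, for example time in ketosis from the daily readings, as a sensitivity covariate. It should not be the main model, because ketosis may itself lie on the causal path.
3. Report the results as hypothesis-generating association only.
4. In the Discussion, replace the aim of establishing a microbiome role with: *explore whether marker change is associated with symptom change within arms*. Align the closing biomarker sentence with it.

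The cost is analysis work and wording, with no new data. Fewer associations will reach significance. Arm adjustment does not remove confounding by adherence, and a measured adherence covariate may remove it only in part, so step 3 is needed whatever the model shows.
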